#### Guolin Qigong

Participants in the intervention group will attend a 2-hour supervised face-to-face (F2F) GQ training class for 12 weeks with home-practice on non-class days. There will be 2 training classes per week for the first 2 weeks and once per week for the next 10 weeks.

The GQ training involves a modified version of a Chinese medical qigong therapy often referred to as “walking qigong” developed by Guo Lin.^
38
^ GQ was developed specifically for cancer and consisted of several breathing and moving exercises. The GQ training in the current study includes the following 3 main exercises:

1. Feng Hu Xi Zhi Ran Xing Gong (Natural Wind Breathing Walking)

Participants walk in a circle, synchronizing their breathing, arm movements, and steps focusing on the movement of their body with the goal of calming one’s mind, relaxing various parts of the body and the mind, and revitalizing the “life-force,” that is, *qi*.

2. Dian Bu Gong (Step Tap Method)

A modified natural Wind Breathing Walking Exercise with additional step tap.

3. Sheng Jiang Kai He Fa (Ascending, Descending, Opening, and Closing Method)

A calming and relaxation method of synchronized arms and legs movements on the spot which can be practiced within limited space.

Each main exercise has to be practiced separately as individual sets comprising 3 parts:

a. Preparatory relaxation exercise (gentle breathing and meditation; 4 minutes):

In relaxed standing posture, synchronize the breath with gentle arm movements in front of the abdomen (opening and closing of the Dantian). Dantian is a Chinese medicine concept that refers to the “elixir field” or “energy center.” It has different locations but often referred to the lower abdomen between the navel and pubic bone of the human body.^73,74^

b. Main exercisei. Feng Hu Xi Zhi Ran Xing Gong (Natural Wind Breathing Walking) orii. Dian Bu Gong (Step Tap Method) oriii. Sheng Jiang Kai He Fa (Ascending, Descending, Opening, and Closing Method).c. Concluding exercise: breathing exercises, opening, and closing of the Dantian, and self-massage (3-6 minutes).^
50
^

Please refer to Supplemental Material 2 for detailed steps. All movements will include modifications to enhance safety. Participants will be advised to rest as and when necessary, according to their health status.

The F2F GQ class will be taught by qualified GQ instructors who are both long-term cancer survivors with more than 20 years of GQ training experience to ensure the full potential of the GQ intervention. The Researcher, who is a registered Chinese Medicine practitioner in Malaysia and Australia with more than 20 years’ experience in Qigong, will be in attendance during the F2F GQ class to ensure the safe and seamless facilitation of the training session.

Home practice is recommended for non-class days according to individual health status and available time.^
54
^ Participants will be provided with class notes and video links (Supplemental Material 3) to promote and support home practice. Home practice after the intervention period is encouraged for incorporation into daily life to foster a healthy lifestyle.

### Usual Care Waitlist Control

Participants in the usual care waitlist control group will be advised to continue with their usual care routines and exercises and will be asked not to attend any other Qigong exercises. They will be offered to attend the same GQ training class after Week-16 of the GQ training of their cohort.

However, to maintain integrity of the study, instructors will not be informed about the allocation of participants. Consequently, when instructors commence training of subsequent cohorts, they will be unaware of which participants belong to the intervention group (commencing from Week 1), and which are part of the control group (joining the GQ group in Week 1), given the GQ training will be offered continuously. This ensures the instructors are effectively blinded to the allocation to maintain impartiality in the delivery of the training and minimizes any potential biases that may arise from instructor knowledge of group allocation.

### Study Assessments

The variables under consideration will encompass basic demographic data, primary outcomes, and secondary outcomes. Basic characteristics will be collected at baseline (Week-1).

Primary feasibility outcomes on adherence, attendance, and any adverse events will be recorded throughout the intervention period from Week-1 to Week-12 in the practice diary by the participants. Secondary patient-reported outcomes on fatigue, depression, and sleep will be measured at baseline (Week-1), mid-intervention (Week-6), post-intervention (Week-12), and 4 weeks after completion of intervention (Week-16). Urine samples (for urine cortisol test) to assess 24-hour urinary cortisol will be collected a day prior to enrollment date and post-intervention (Week-12). Primary feasibility outcomes and secondary patient-reported outcomes will be assessed by an independent research assistant to minimize bias. A summary of the planned data collection is shown in Figure 2.

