It is feasible for cancer survivor participants to engage in the GQ training and those who participated in the GQ training will experience positive impacts on CRF, sleep, depression, and cortisol level. Feasibility of this study is established at about 80% to 85% retention rate and 75% to 85% class attendance rate based on prior similar studies.^63
[Bibr bibr64-15347354241252698]-65^The semi-structured interview will identify a broader spectrum of benefits and barriers to participation and adherence to GQ training to provide valuable insights for program enhancement.

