#### Feasibility outcomes

Feasibility will be assessed based on recruitment rate, retention rate, class attendance, home practice adherence, the nature and extent of missing data, and safety. Safety will be monitored and assessed based on total number of Adverse Event and the presence of any Serious Adverse Event.^
75
^

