### Trial Monitoring

The Researcher will report progress of the trial to the panel of supervisors on a quarterly basis. Annual reports will be submitted to the human ethics committee to monitor the trial progress and outcomes. Participants in the GQ group will be advised to record any perceived adverse events in the practice diary and this will be recorded in participants’ Adverse Event Form by the Researcher. The severity, expectedness and causal relationship with GQ intervention will be assessed for every adverse event according to guidelines for safety reporting.^75,87^

The schedule of the enrollment, intervention, and data collection is shown in Figure 2.

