### Data Collection

De-identified information will be collected and managed by assigning an identification code to each participant. Demographic information, medical history, any occurrence of adverse events, practice adherence and intervention outcomes during the study will be collected and recorded on paper or electronic file.

Demographic information and medical history will first be collected by the Researcher. De-identified Practice Diary, Brief Fatigue Index, Pittsburgh Sleep Quality Index, and Centre for Epidemiologic Studies Depression will be collected at Week-1, Week-6, Week-12, and Week-16, while the 24-hour urine cortisol results will be collected by the research assistant at Week-1 and Week-12. Interviews will be conducted by the Researcher after Week-16, audio-recorded, de-identified, and transcribed verbatim.

During the study, all data will be recorded in participant source document files in paper format (sociodemographic data, feasibility and clinical data), administered by independent research assistants and will be transferred to an electronic format for storage and analysis. The 2 independent research assistants will verify and check the data collected by each other. After all data are confirmed and checked the research assistants will extract the data into an Excel sheet for analysis.

After participants have been randomized, dropout and premature termination or withdrawal from the 2 groups at any point will be recorded along with relevant reasons. Participants can choose to withdraw and will not be affected at any time while declining to participate or withdrawing from the trial. In some cases, participants will discontinue the intervention, such as illness, progression of their disease, or inability to engage despite adjustment of the program. Participants who withdraw from the intervention during the trial will not be replaced.

Interviews will be conducted after Week-16 in person or online via Zoom by the Researcher at an appointed time. Interview sessions will be audio recorded and transcribed verbatim using NVivo or the recording feature available in Zoom, ensuring accurate documentation, and stored in electronic files for analysis.

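### Attendance and adverse events rest on a participant-kept diary, and the only stated instruction to record events goes to the Guolin Qigong (GQ) arm: attendance can be overestimated and safety lacks a like-for-like background rate

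*Protocol article*

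**What the plan says.** The Abstract and the section Feasibility outcomes make class attendance and safety part of the primary outcome. Study Assessments names the source: adherence, "attendance, and any adverse events will be recorded throughout the intervention period from Week-1 to Week-12 in the practice diary by the participants". No other source for attendance is named, although under Guolin Qigong the Researcher "will be in attendance during the F2F GQ class to ensure the safe and seamless facilitation of the training session".

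For safety, Feasibility outcomes states: "Safety will be monitored and assessed based on total number of Adverse Event and the presence of any Serious Adverse Event". Trial Monitoring gives the recording instruction: "Participants in the GQ group will be advised to record any perceived adverse events in the practice diary". The Researcher transfers these entries to an Adverse Event Form, and each event is assessed for severity, expectedness and causal relationship with GQ. Data Collection adds that "any occurrence of adverse events, practice adherence and intervention outcomes during the study will be collected", without naming an arm or a method.

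The success criterion stands in the hypothesis at the end of the Background: "Feasibility of this study is established at about 80% to 85% retention rate and 75% to 85% class attendance rate". It gives no denominator for attendance. On the schedule: "There will be 2 training classes per week for the first 2 weeks and once per week for the next 10 weeks".

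On timing, Study Assessments ends diary recording at Week-12. Data Collection says: "De-identified Practice Diary, Brief Fatigue Index, Pittsburgh Sleep Quality Index, and Centre for Epidemiologic Studies Depression will be collected at Week-1", and the sentence goes on to list Weeks 6, 12 and 16.

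**The concern.** There are three weaknesses in how these outcomes are captured.

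- **Safety.** Eligibility runs from newly diagnosed patients to long-term survivors, so events unrelated to GQ are to be expected. A raw count from one arm cannot be set against a background rate, although a randomised control group exists. The causality judgement required for every event then has to be made without its best evidence.
- **Attendance.** A diary entry can be counted only if the diary is kept and handed in. Under Intervention, participants have a few days after learning their allocation to decide whether to go on. Someone allocated to GQ who opts out then attends no class and may never keep a diary. If such people drop out of the calculation, the attendance figure describes those who stayed.
- **Window.** Follow-up runs to Week-16 and home practice is encouraged after the intervention. The two sections differ on whether the diary covers that period.

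At stake are the attendance criterion by which feasibility will be judged, and whether the safety result can be interpreted.

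**Working it through.** The plan derives no figure here that could be reproduced: the 75% to 85% attendance range is a threshold. The check is a sensitivity calculation for attendance and a comparison of sections for safety.

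**Attendance: inputs**
- Classes (Guolin Qigong): 2 × 2 + 10 × 1 = 14.
- GQ arm (Sample Size): 30 participants.
- Dropout (Sample Size): about 20%, so 0.20 × 30 = 6 leave and 24 complete. The retention criterion in the Background is about 80% to 85%.
- Assumed, because the article gives no values: attendance among completers of 80%, and among dropouts of 0%, 25% or 50% of the 14 classes.

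**Formula**

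Attendance over all randomised = r × a + (1 − r) × x, where r is retention, a is attendance among completers and x is attendance among dropouts. If dropouts' diaries were absent, the reported figure would simply be a.

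| r | a | x = 0% | x = 25% | x = 50% |
|---|---|---|---|---|
| 0.80 | 0.80 | 0.64 + 0.00 = 64% | 0.64 + 0.05 = 69% | 0.64 + 0.10 = 74% |
| 0.85 | 0.80 | 0.68 + 0.00 = 68% | 0.68 + 0.0375 = 71.75% | 0.68 + 0.075 = 75.5% |

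In five of the six cells a reported 80% would correspond to less than 75% over everyone randomised to GQ.

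Turned round, the completer attendance needed for 75% overall is a = (0.75 − (1 − r) × x) / r:
- r = 0.80: 0.75/0.80 = 93.8%; 0.70/0.80 = 87.5%; 0.65/0.80 = 81.2%.
- r = 0.85: 0.75/0.85 = 88.2%; 0.7125/0.85 = 83.8%; 0.675/0.85 = 79.4%.

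**How far this depends on the assumptions**

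Take 24 completers at 85%. If the six dropouts attended 4 of 14 classes each, the overall figure is (24 × 0.85 + 6 × 4/14)/30 = 73.7%. At 5 of 14 it is (24 × 0.85 + 6 × 5/14)/30 = 75.1%. One class per dropout moves the result across the floor.

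**Safety: sections side by side**
- Study Assessments refers to participants generally, but the instrument is a practice diary.
- Usual Care Waitlist Control asks controls not to attend other Qigong and says nothing of a diary.
- Trial Monitoring addresses the GQ group and perceived events only.
- Data Collection covers events during the study without an arm or a method.

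Anyone following these sections has a procedure for GQ participants and none for controls.

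**Window**

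Recording to Week-12 and diary collection at Week-16 can both hold only if the last collection brings in no new entries or if recording in fact continues. The article does not say which.

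**The case against.** The strongest reply is that a reader might infer four things which the documents do not establish.

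1. *That attendance is inflated.* No section leaves out dropouts' diaries or sets a completer denominator. Quantitative Data states intention to treat. Data Collection records withdrawals in both groups with reasons and collects diaries at Week-6, so partial diaries may exist. If missing entries were counted as absences, the error would go the other way. All this stands, so the point is a risk and not a demonstrated bias. Still, intention to treat with last observation carried forward does not fix an attendance denominator, and the outcomes named for the model are the questionnaire scores and cortisol.
2. *That events are recorded in the GQ arm only.* This is an inference from Trial Monitoring. Study Assessments and Data Collection are worded generally, and an article may leave operational detail to the full protocol. What stands is that the one procedure described is for the GQ arm.
3. *That the trial cannot attribute events.* Trial Monitoring provides a causality assessment for each event, and Feasibility outcomes defines safety as a count and the presence of serious events, not as a contrast between arms. No stated analysis fails. A comparator would strengthen attribution; its absence does not rule attribution out.
4. *That recording definitely stops at Week-12.* Data Collection points the other way. The two sections need reconciling, no more.

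Two further replies deserve weight. An independent research assistant assesses the feasibility outcomes, and two assistants check each other's data; that guards against transcription and assessor error but cannot recover entries never made. And the separate retention criterion already reflects dropout, so attendance among those who stay is a legitimate quantity. That is a reason to report both figures, each with its denominator.

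**Conclusion.** The concern holds as a weakness in data capture that is cheap to mend. A participant-kept diary is the only named source for two primary feasibility outcomes, at classes where the Researcher is already present. The only stated instruction to record adverse events is to the GQ group, and the article's two statements on the diary's end differ. Read as written, safety becomes a one-arm count of perceived events, and attendance can be overestimated if diaries are missing for those who leave or opt out.

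The possible size matters for the feasibility verdict. An 80% figure among completers could stand for 64% to 74% of all randomised at 80% retention, or 68% to 75.5% at 85%, against a floor of 75%. These ranges rest on assumed attendance among completers and dropouts, and on dropouts' diaries not being used, which the article neither says nor excludes. The documents do not support the stronger conclusions that attendance is inflated or that control-arm events will go unrecorded.

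**What to change.** (a) Take attendance from a register completed at each class and checked by the independent research assistant. Report it over 14 classes × all randomised to GQ (14 × 30 = 420 class places at the planned size), with classes after withdrawal or opt-out counted as not attended. Give attendance among completers as a secondary figure. Keep the diary for home practice and as supplementary information on events.

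(b) Ask both arms the same structured adverse-event question at Weeks 6, 12 and 16, when questionnaires are already completed. Report events per arm with a 95% confidence interval for the difference, and call it imprecise. With 30 per arm and, as a worst case, half of each arm having an event, the half-width is 1.96 × √(2 × 0.5 × 0.5/30) = 0.253, about 25 percentage points.

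(c) Reconcile the Week-12 end of diary recording in Study Assessments with the Week-16 diary collection in Data Collection.

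The cost is one register sheet and one form item, with no added visits or staff. Recruitment began in October 2022, so participants already past these assessments will have been followed under the old method. That mixed ascertainment should be reported as a limitation.

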**Figure 2. fig2-15347354241252698:**
[figure not shown]
Schedule of enrollment, intervention and data collection Abbreviations: BFI, Brief Fatigue Inventory, CES-D, Centre for Epidemiologic Studies Depression; PSQI, Pittsburgh Sleep Quality Index.

#### Basic demographic data

Participants’ basic characteristics (sex, marital status, age) and cancer history will be collected using a self-designed questionnaire.

#### Feasibility outcomes

Feasibility will be assessed based on recruitment rate, retention rate, class attendance, home practice adherence, the nature and extent of missing data, and safety. Safety will be monitored and assessed based on total number of Adverse Event and the presence of any Serious Adverse Event.^
75
^

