### Sample Size

Using a small effect size (0.2)^
65
^ rather than a medium effect size (0.5)^
64
^ to achieve a more conservative estimation, the sample size is 25 cases in each group with 90% power and two-sided 5% significance trial design.^
88
^ Allowing for a drop-out of about 20% based on previous studies,^89
[Bibr bibr90-15347354241252698][Bibr bibr91-15347354241252698]-92^ a total sample of 60 (30 in each group) would be required.

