## Limitations

The nature of the intervention precludes blinding of both participants and researcher. While the researcher remains unblinded as this trial is open-label, the instructors will not be aware of intervention allocation to minimize bias. Although including cancer survivors across all stages enables a diverse assessment of feasibility, it potentially limits the generalizability of the results though sub-group analysis will be conducted. Furthermore, the reliance on self-reported data for secondary outcomes emphasizes the necessity for incorporating objective measures like actigraphy, polysomnography, and established scales such as the Hamilton Depression Rating Scale to ensure a comprehensive evaluation of GQ’s impact on CRF, sleep quality, and depression. Additionally, the predominant participation of Asian Chinese individuals highlights the need for expanded research to comprehend GQ’s feasibility and effects among cancer survivors from various ethnic and racial backgrounds. These limitations underscore the challenges inherent in the study’s design and demographics, emphasizing the importance of integrating objective measures and broadening participant diversity for more conclusive and inclusive findings.

Despite the limitations, exploring GQ as a potential intervention to address existing gaps in effective treatment for CRF and its related symptom cluster of sleep quality and depression in cancer survivors demonstrates a forward-thinking approach in the field of oncology. It expands on the knowledge base and promotes innovative thinking, fostering the development of novel interventions with potential contribution to the advancement of oncology care.

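### The safety part of the primary feasibility outcome is an event total plus an any-SAE indicator, with no participant denominator and without the severity and causality grading collected for every event

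*Protocol article*

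**What the plan says.** The Feasibility outcomes section lists six components of the primary outcome: recruitment, retention, class attendance, home practice, missing data and safety. It then fixes how safety is measured: "Safety will be monitored and assessed based on total number of Adverse Event and the presence of any Serious Adverse Event".

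Trial Monitoring describes a fuller assessment of each event: "The severity, expectedness and causal relationship with GQ intervention will be assessed for every adverse event according to guidelines for safety reporting". It places the recording duty on one arm: "Participants in the GQ group will be advised to record any perceived adverse events in the practice diary". Data Collection is more general and names no arm: "any occurrence of adverse events, practice adherence and intervention outcomes during the study will be collected". Study Assessments gives the window: "any adverse events will be recorded throughout the intervention period from Week-1 to Week-12".

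The Inclusion Criteria admit survivors from new diagnosis to long-term survivorship and require a life expectancy of more than 3 months. Data Collection foresees that some participants will discontinue because of illness or disease progression. At the end of the Background, numerical feasibility benchmarks are set for retention and class attendance only. The Quantitative Data section does not mention safety.

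**The concern.** The article states a measure for a component of the primary outcome, and that measure suits this population poorly.

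- **No participant denominator.** One ill participant who logs ten events gives the same total as ten participants who are each hurt once by the exercise. For a judgement about an exercise programme, these two results mean very different things.
- **No attribution.** An admission for disease progression makes a serious event present just as an injury in class would.
- **Grading not carried in.** The information that would separate these cases is collected under Trial Monitoring but forms no part of the outcome as defined.

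A harmless programme could therefore look worrying. A small cluster of GQ-related injuries could also be hard to see inside a total made up mostly of disease and treatment events.

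**Working it through.** The plan gives no safety rate, threshold or precision, so there is no stated figure to reproduce. The calculations below are illustrations.

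**Inputs from the article**
- GQ participants: 30 (Sample Size: "a total sample of 60 (30 in each group) would be required").
- Recording window: Week 1 to Week 12 (Study Assessments).

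**Inputs assumed**
- Risk p of at least one SAE from any cause, per participant, over the window: 1%, 2%, 5% or 10%, with participants independent and GQ causing none.
- Background AEs per participant: 0.5 to 2. GQ-related AEs per participant: 0.1.

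**1. Any-SAE indicator.** The chance that it is positive among n participants is 1 − (1 − p)^n. With n = 30:

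| Assumed p | (1 − p)^30 | Chance of at least one SAE |
|---|---|---|
| 1% | 0.740 | 26% |
| 2% | 0.545 | 45% |
| 5% | 0.215 | 79% |
| 10% | 0.042 | 96% |

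If events were captured equally in both arms and the indicator covered all 60, the values for 2%, 5% and 10% would be 70%, 95% and 99.8%. Equal capture is not clear from the text, so the figures for 30 are the safer ones to use.

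**2. The same indicator restricted to GQ-related SAEs.** If the true related risk is 0, 0.1%, 0.5% or 1%, the chance of at least one among 30 is 0%, 3%, 14% or 26%. This version responds to GQ harm, provided that attribution is correct.

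**3. Event total.** The expected total is 30 × (background + related).
- Background 0.5: 30 × (0.5 + 0.1) = 18 events, of which 0.5/0.6 = 83% are background.
- Background 2: 30 × (2 + 0.1) = 63 events, of which 2/2.1 = 95% are background.

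**4. What 30 participants can show.** With 0 related SAEs in 30, the exact one-sided 95% upper bound is 1 − 0.05^(1/30) = 9.5%. The upper limit of the two-sided exact 95% interval is 1 − 0.025^(1/30) = 11.6%.

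**5. The two sections side by side.** Feasibility outcomes defines what is counted, and Trial Monitoring defines how each event is judged. Both cite the same safety-reporting reference. Neither says that the judgement enters the outcome, and neither says that it is left out of the report.

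**The case against.** **Nothing is decided by the count.** A reader might infer that background morbidity determines the safety verdict. The article does not support that: its benchmarks cover retention and attendance only, and no conclusion or pass mark is attached to the AE total or to the presence of an SAE. This objection stands. The probabilities above show how uninformative the indicator can be, not how often the trial would fail.

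**The grading is used.** A reader might also infer that the causality grading is collected and then ignored. That goes too far as well. Trial Monitoring applies it to every event for monitoring and safety reporting. What remains is narrower: the grading is not carried into the stated outcome.

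**Tabulation belongs in an analysis plan.** An article need not specify safety tables, and the individual Adverse Event Forms would let an analyst tell the cases apart. This is fair for layout. It does not cover an outcome definition that the article itself states for a primary component.

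**The size is assumed.** The documents give no SAE rate, and the Exclusion Criteria remove several groups at higher risk, including those who cannot walk and those for whom participation would be unsafe. This stands. The figures are conditional on the assumed range and do not predict a positive indicator.

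**Related-only reporting has its own weakness.** All-cause counts do not depend on anyone's judgement. Here the Researcher completes the Adverse Event Forms, is unblinded (Limitations) and is an experienced Qigong practitioner; the article does not name who assigns causality. This stands too, and it shapes the remedy.

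**Conclusion.** The point holds as a weakness in a stated measure. The safety component of the primary outcome is a raw event total plus an any-SAE indicator. It has no participant denominator and makes no use of gradings that the trial already collects. In this population, background events can dominate the total and make the indicator positive without harm from GQ.

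The size rests wholly on assumed rates. At 2% to 10% SAE risk per participant, independent between participants, the indicator is positive in 45% to 96% of trials with 30 GQ participants and no GQ harm; at 1% it is 26%. No safety threshold turns on it, so what is lost is interpretability.

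Comparison with the control arm might show the background level, but the diary instruction names the GQ group only and the general collection statement names no arm. Control-arm capture is therefore unclear. The change is worth making because it is cheap and uses existing data.

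**What to change.** Restate the safety outcome in Feasibility outcomes as the number and percentage of participants with at least one:

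1. AE;
2. GQ-related AE;
3. SAE;
4. GQ-related SAE.

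Give each an exact 95% interval and state the denominator. Take relatedness and severity from the assessment already described in Trial Monitoring, and cross-refer to it. Show all-cause and related results side by side, and do not rest the safety conclusion on related events alone, because attribution in an open-label trial may be biased. Keep the total number of events as a descriptive line.

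The cost is a change of wording and one more safety table. No new data are needed in the GQ arm, since the gradings are already collected there. The intervals will be wide: 0 of 30 still leaves a one-sided 95% upper bound of about 9.5%. Showing that limit also guards against false reassurance from a clean result.
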